#### Routine assessments

Systolic (SBP) and diastolic (DBP) blood pressure (mmHg) will be measured with the patient sitting on a chair with back support, while HR_rest_ will be recorded as the average of the last minute out of 10 min of supine rest [49].

### Research staff training

The medical personnel will receive specific training on how to approach to and communicate with the patients to maximize the enrollment rate throughout the recruitment process of the trial. The training will provide the healthcare professionals with standardized information that they can share with the patients, fostering effective communication, particularly as regards the trial aims, allocation procedure and intervention protocol.

All the investigators will undergo several training sessions specifically designed to familiarize them with the timing and protocols of all the trial assessments, and the correct procedures to enter and store patients’ data in the WBA.

Exercise specialists will receive training on how to implement and monitor the exercise prescription in the patients of the intervention arm and on how to input data and query the exercise session database within the WBA. They will be also informed about the risks associated with exercise in older T2D patients and trained on how to recognize the signs and symptoms that call for the immediate termination of the exercise session [34].

### Patients training

All patients will receive training on how access the WBA, retrieve their own data, and enter lifestyle information. Patients of the intervention arm will also be instructed how to enter data of exercise sessions not performed under the supervision of the exercise specialists into the WBA.

### Additional information on data collection, management, and retention

The information collected during the trial will be depersonalized and password-protected, and access to data will be restricted to the TRIPL-A staff in accordance with current Italian law (art 13 D.lgs.196/2003). The complete final dataset will contain no identifying participant information and its access will only be granted to TRIPL-A principal investigators.

Paper-based CRFs will be used to record the results of patient assessments at each time-point (see Fig. 1). CRFs data will also be entered into the WBA to provide the information required to design an exercise prescription tailored to the specific needs of each patient throughout the trial. This will also provide the trial with both a data accuracy verification procedure (the WBA will warn the user when data entry is incorrect or not physiologically plausible and when missing data are missing) and an electronic back-up.

### Statistical methods

#### Sample size calculations

The sample size has been calculated to test the hypothesis of no difference in sitting time per day between intervention and control arms at the 12-month time-point (2-sided independent sample t-test; statistical power 0.8; α level of significance 0.05; 1:1 ratio between intervention and control arm). Given an expected mean value of sitting time of 500 ± 200 min per day [39, 41–43], a sample size of 112 participants in each arm will be necessary to detect a difference of 75 min per day of mean sitting times between intervention and control arm. Therefore, it was assumed that a sample size of 300 participants, i.e. 120 in each arm accounting for an expected drop-out rate of 20%, is appropriate to obtain the desired statistical power.

Sample size was computed using STATA statistical software (StataCorp).

#### Data analyses

*Intention to treat* analysis will be adopted to account for possible issues related to noncompliance and missing outcomes. Data quality and internal consistency will be assessed *ex-post* using Cronbach’s alpha. In addition, automatic routines will be performed on the data to detect possible outliers, which will be excluded from further analyses. Explorative univariate and bivariate data analyses will then be performed.

For each study outcome, the intervention and control arm will be compared, as the difference between baseline and 12-month time-point, using independent sample t-tests. A mixed-design ANOVA will be used to compare each study outcome between intervention and control arm at the four different time-points, followed by *post-hoc* pairwise comparisons when a significant interaction is found. Participants’ characteristics (e.g., age, sex, fitness status, physical activity level, and metabolic profile) will be used as covariates, and appropriate interaction terms will be assessed and may be included in the model. For all tests, 2-sided *p* values with an α level of significance of 0.05 will be used. Bonferroni’s criterion will be used to adjust the overall α level to correct for multiple tests.

The assumptions of each statistical test will be assessed before analyses and, if not met, either data transformation will be performed or alternative statistical methods will be adopted (e.g., GEE, mixed-models, non-parametric analyses, etc.) will be performed. The residuals and goodness of fit of the models will also be examined.

SPSS Statistics (IBM) and R (R Core Team) software will be used to perform data analyses.

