#### Primary outcome measure

Sitting time will be retrieved from the results of the IPAQ short form and computed as average daily minutes of sitting calculated over a one-week period. The IPAQ is a well validated tool [39–43] for assessing both habitual sitting time and physical activity engagement. The IPAQ short form will be interview-administered by trained personnel.

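### Every automatically flagged outlier is excluded, confirmed error or not, which conflicts with the intention-to-treat analysis adopted in the same paragraph

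*Protocol article*

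**What the plan says.** In the protocol article, the Data analyses section opens with intention to treat: the "analysis will be adopted to account for possible issues related to noncompliance and missing outcomes". The next sentence announces an assessment of data quality with Cronbach's alpha. The one after it says that "automatic routines will be performed on the data to detect possible outliers, which will be excluded from further analyses". The exploratory analyses, the between-arm comparison at 12 months ("as the difference between baseline and 12-month time-point, using independent sample t-tests") and the mixed-design ANOVA all come after that step.

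The primary outcome is interview-reported sitting time, "computed as average daily minutes of sitting calculated over a one-week period" (Primary outcome measure).

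Entry errors have a separate safeguard. In the section on data collection, management and retention, "the WBA will warn the user when data entry is incorrect or not physiologically plausible".

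The article gives no detection rule or threshold. It does not say whether flagging is done within arm or on the pooled sample, and it requires no check against the case report form (CRF). It also states no analysis with the flagged values retained.

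**The concern.** Intention to treat means that randomised patients are analysed with the outcomes observed on them. The outlier step removes outcomes because of their value, so it creates missing data that depend on the outcome itself. A genuine large responder or a genuine very long sitter is treated in the same way as a typing error.

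The primary comparison is affected in one of two ways:

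- **Flagging within each arm.** Trimming shrinks the estimated SD, but the t-test treats the trimmed samples as complete. The standard error is too small and the type I error rises.
- **Flagging on the pooled sample.** The fences are centred between the arms. If the intervention works, they cut more low values from the intervention arm and more high values from the control arm, so the difference moves toward zero.

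Because the rule is open, several thresholds and two flagging bases fit the text, and each can give a different primary result.

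**Working it through.** **Inputs from the article (Sample size calculations).** "2-sided independent sample t-test; statistical power 0.8"; "α level of significance 0.05"; "expected mean value of sitting time of 500 ± 200 min per day"; a difference of 75 min/day; 300 enrolled at 1:1 with 20% drop-out.

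**The plan's own figure.** n per arm = 2(1.960 + 0.842)² × 200² / 75² = 2 × 7.849 × 40,000 / 5,625 = 111.6, so 112, as stated. Analysed n = 300 × 0.8 / 2 = 120 per arm. Power at 120 per arm: SE = 200√(2/120) = 25.8; 75/25.8 − 1.96 = 0.945; power 0.83.

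**Assumptions, not in the documents.** Four detection rules: 3×IQR fences, 3 SD, 1.5×IQR fences and 2 SD. Two shapes: normal, and gamma with shape (500/200)² = 6.25 and scale 200²/500 = 80. The SD of 200 is applied to the analysed variable.

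**Simulation.** 120 per arm, pooled-variance t-test, 2-sided 0.05, 20,000 trials per cell (Monte Carlo standard error about 0.0015 at 0.05). With no exclusion, the type I error is about 0.05, the estimate 75 min and power 0.82–0.83. With exclusion (ranges run from normal to gamma data):

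| Rule | Type I error, flagged within arm | Estimate of a true 75 min, flagged pooled |
|---|---|---|
| 3×IQR | about 0.05 | about 75 |
| 3 SD | 0.06–0.07 | 72–73 |
| 1.5×IQR | 0.07–0.09 | 69–71 |
| 2 SD | 0.09–0.11 | 59–64 |

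Repeat runs put the gamma figure for 1.5×IQR within arm between 0.090 and 0.100. Pooled flagging keeps the type I error near 0.05. Within-arm flagging leaves a uniform 75-min shift essentially unbiased.

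**Hand check of one cell (normal, pooled, 2 SD).** Put the arms at ±37.5 around their midpoint. Pooled SD = √(200² + 37.5²) = 203.5, so the fences lie at ±407.0. For the intervention arm the standardised limits are (−407.0 + 37.5)/200 = −1.847 and (407.0 + 37.5)/200 = 2.222. The truncated mean moves by 200 × (0.0725 − 0.0338)/0.9545 = 8.1 min toward the centre. The control arm moves equally the other way. Estimate: 75 − 2 × 8.1 = 58.8, in line with the simulated 59.

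**Effect concentrated in a few responders (assumed).** Let 20% of intervention patients change by −375 min, so the mean effect is 0.20 × 375 = 75. Under pooled 1.5×IQR exclusion:

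- change-score SD 200: about 60 min
- change-score SD 160: about 54 min
- change-score SD 120: about 36 min

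If sitting time has SD 200 at each visit, the change-score SD is 200√(2(1 − ρ)). SD 200 then means a correlation ρ = 0.50 between visits, and SD 120 means ρ = 1 − 120²/(2 × 200²) = 0.82. The article gives no ρ.

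**The case against.** **It may be error screening.** The clause follows directly on a sentence about data quality, so catching errors is a plausible purpose, and a condensed article may leave the detection rule to a fuller document. That stands for the rule. It does not stand for the exclusion, which the article states without condition, so an analysis plan consistent with it would carry the conflict forward.

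**It may mean data points, not patients.** That reading is possible, and other visits could then stay in. But a patient without a usable baseline or 12-month value has no change score, so the observed value still drops out of the primary t-test.

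**Analysts work with coded arms.** The Enrollment and arm assignment section provides for this, and it limits knowing manipulation. It does not prevent flagging within each coded arm.

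**Assumption failures are already handled.** The article allows transformation or non-parametric methods. In the order given they come after exclusion, so they help only in part. They do show that deletion is not needed to cope with skewed data.

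**Stronger readings that the documents do not support:**

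- A reader might infer that entry errors are already caught, so that whatever is flagged is mostly genuine. The article says only that the web-based application warns the user. It does not say that entries are blocked or corrected, and sitting time is recalled at interview, so errors and misreports can remain.
- A reader might infer material harm under any rule. With 3×IQR fences there is almost none.
- A reader might take the fall from 75 to 36 min as following from 500 ± 200. It needs an assumed change-score SD of 120; at SD 200 the figure is about 60.
- A reader might expect power always to fall. Pooled 1.5×IQR exclusion takes it from about 0.83 to 0.80 in normal data but leaves it at 0.83–0.84 in gamma data, although the estimate still shrinks.

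**Conclusion.** The conflict in wording is certain: the paragraph adopts intention to treat and then commits to removing observed outcomes on the strength of an automatic flag, with no step that separates errors from genuine extremes. The size of the consequence is uncertain, because it depends on a rule and a flagging basis that the article does not state. Under the assumptions above it runs from nothing noticeable (3×IQR), through small (3 SD), to a doubled type I error or a loss of 11 to 16 of the 75 min (2 SD). The two harms largely belong to different implementations and should not be added together.

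This should be fixed before the data are analysed. Because the harm depends wholly on an unstated rule, it falls short of a defect that would by itself invalidate the primary result.

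**What to change.** Replace the exclusion clause in Data analyses with:

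> Extreme values are queried against the CRF without knowledge of arm. Only confirmed errors and impossible values (for example, sitting time above 24 × 60 = 1,440 min/day) are corrected or set to missing. All other values stay in every intention-to-treat analysis. A robust or rank-based sensitivity analysis is reported.

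With all values kept, the simulated type I error returns to about 0.05, the estimate to 75 min and power at 120 per arm to about 0.82–0.83. The cost is one changed sentence and a little query work. Paper CRFs are already kept for each assessment, so no new data or visits are needed.

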**Methods:**

A randomized controlled design will be used, and an ERS, supported by a WBA, will be implemented. 300 physically inactive T2D patients (aged 65–74 years) will be assigned to either an intervention or control arm. Control arm patients will only receive behavioral counseling on physical activity and diet, while intervention arm patients will also undergo an 18-month (3 day/week), discontinuously supervised aerobic exercise training program. The trial will be divided into six three-month periods: during first, third and fifth period, an exercise specialist will supervise the training sessions and, using the WBA, prescribe exercise progression and monitor exercise adherence. Patients will exercise on their own in the other periods.

Patients’ sedentary behaviors (primary outcome), PA level, fitness status, metabolic profile, psychological well-being, quality of life, and use of health care services (secondary outcomes) will be assessed at baseline and at 6, 12, and 18 months from baseline.

Repeated measure ANCOVAs will be used to compare the intervention and control arm with respect to each study outcome measure.

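### The 12-month t-test on change from baseline is not the test the trial was sized for, and the plan does not say whether it or the covariate-adjusted ANOVA decides the trial

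*Protocol article*

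**What the plan says.** All references are to the protocol article.

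- **Sample size calculations.** The trial is sized to "test the hypothesis of no difference in sitting time per day between intervention and control arms at the 12-month time-point", with these settings: "2-sided independent sample t-test; statistical power 0.8; α level of significance 0.05; 1:1 ratio between intervention and control arm". The spread is that of a sitting-time value: "Given an expected mean value of sitting time of 500 ± 200 min per day". The target effect is 75 min/day between the arm means, and the conclusion is that "a sample size of 112 participants in each arm will be necessary".
- **Assessments/outcomes.** The between-arm difference at 12 months is the main outcome for every measure.
- **Data analyses.** The 12-month comparison is a t-test on change: "For each study outcome, the intervention and control arm will be compared, as the difference between baseline and 12-month time-point, using independent sample t-tests". The section then gives a mixed-design ANOVA over the four time-points. Pairwise comparisons follow if the interaction is significant, and participant characteristics serve as covariates. Neither analysis is called primary.
- **Abstract, Methods.** Only one method is named: "Repeated measure ANCOVAs will be used to compare the intervention and control arm with respect to each study outcome measure".

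**The concern.** The sample size section and the analysis section describe different tests of the same main outcome. In a randomised trial a difference in 12-month means and a difference in mean change estimate the same effect, but their variances differ. The 0.80 power computed for one does not automatically apply to the other. Whether it does depends on how strongly a patient's 12-month sitting time correlates with the baseline value, and the article is silent on that.

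Two things are at stake. First, if the correlation is modest, the change-score test has less power than stated. Baseline sitting time, which is collected anyway, could be used more efficiently as a covariate. Second, the t-test and the mixed-design ANOVA can give different answers. With neither named as primary, the result on which the trial rests is not fixed in advance.

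**Working it through.** **Inputs.** From Sample size calculations: difference 75 min/day, SD 200, two-sided α 0.05, power 0.80, 1:1 allocation, and 300 randomised to leave 120 per arm after 20% drop-out (150 × 0.8 = 120). *Assumptions:* the correlation r is not given, so a range is shown; the SD is 200 at both baseline and 12 months.

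**Step 1: reproduce the stated figure.** n per arm = 2 × (1.960 + 0.842)² × (200/75)² = 111.6, which rounds up to 112. This matches. The t-distribution gives 112.6, a trivial difference. Power for the 12-month value is 0.798 at 112 per arm and 0.825 at 120 per arm. So 112 is right for a test of 12-month values with SD 200.

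**Step 2: SDs for the other two analyses.**

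- Change score: 200 × √(2(1 − r)). This equals 200 only at r = 0.5.
- ANCOVA residual: 200 × √(1 − r²).
- Variance ratio, ANCOVA to change score: (1 − r²) / (2(1 − r)) = (1 + r)/2.

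**Step 3: power at 120 per arm (noncentral t) and n per arm for 0.80 power (normal approximation).**

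| r | SD change | SD ANCOVA | Power, change | Power, 12-month value | Power, ANCOVA | n per arm, change | n per arm, ANCOVA |
|---|---|---|---|---|---|---|---|
| 0.3 | 236.6 | 190.8 | 0.686 | 0.825 | 0.858 | 157 | 102 |
| 0.4 | 219.1 | 183.3 | 0.752 | 0.825 | 0.884 | 134 | 94 |
| 0.5 | 200.0 | 173.2 | 0.825 | 0.825 | 0.916 | 112 | 84 |
| 0.6 | 178.9 | 160.0 | 0.899 | 0.825 | 0.951 | 90 | 72 |
| 0.7 | 154.9 | 142.8 | 0.962 | 0.825 | 0.982 | 67 | 57 |

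**Step 4: break-even points.** At 120 per arm the change-score test reaches 0.80 power when r is about 0.467. It overtakes the test of 12-month values when r exceeds 0.5. At r = 0.3 it would need 157 per arm, more than the 150 to be randomised per arm.

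**Step 5: does 300 suffice for ANCOVA?** Its requirement is largest at r = 0, where the residual SD is 200 and n is 112 per arm. The plan expects 120 evaluable per arm, so 300 is enough at every non-negative r.

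**Step 6: is ANCOVA strictly better everywhere?** No. With unequal SDs the two tie when the slope of the 12-month value on baseline is 1. For example, take baseline SD 200, 12-month SD 250 and r = 0.8. The change-score variance is 250² + 200² − 2 × 0.8 × 200 × 250 = 22,500, and the ANCOVA variance is 250² × (1 − 0.64) = 22,500. With r very near 1, estimating the slope can make ANCOVA trivially worse (variance ratio about 1.002 at r = 0.995 with 120 per arm).

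**The case against.** A change-score t-test in a randomised trial is unbiased and has the correct type I error. Sizing on a simple t-test is common practice, and the stated 112 is reproduced. For r above 0.5 the planned test has more power than the one sized. All of this stands, so the mismatch means that power is not assured, not that it has been lost.

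Several stronger readings are tempting but not supported:

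- *ANCOVA is always more precise.* It is not: the two tie at a slope of 1.
- *The article plans three conflicting analyses.* The t-test under Sample size calculations is a sizing assumption. The abstract's repeated measure ANCOVAs can be read as the mixed-design ANOVA with covariates from Data analyses. On that reading two planned analyses remain.
- *The covariates will be post-randomisation values, or baseline sitting time is excluded.* The list gives examples of participant characteristics alongside age and sex, which most naturally means baseline values. It is not exhaustive, and nothing says that follow-up values will be used. Baseline sitting time also enters the mixed-design ANOVA as one of its four time-points.

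The objection does not remove two facts. The test sized and the 12-month test planned have different variances, with no r or SD of change to link them. And no analysis is designated as the deciding one. Both concern what the article states, not detail that it might leave to a fuller document.

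**Conclusion.** The point holds in a limited form. The 112 per arm is correct for 12-month values but does not establish 0.80 power for the planned change-score test. That power holds at 120 per arm only if r is at least about 0.47. Over r from 0.3 to 0.7 it runs from 0.69 to 0.96, against 0.86 to 0.98 for baseline-adjusted ANCOVA. These figures assume equal SDs of 200, α of 0.05 and the 20% drop-out stated. Since r is unknown, a shortfall is possible but not demonstrated.

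The planned t-test is valid, and the case against it is one of efficiency. In large samples ANCOVA is at least as precise and usually more so, at no cost. Separately, the choice between the change-score t-test and the mixed-design ANOVA as the deciding analysis is left open and should be settled.

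**What to change.** Name one primary analysis under Data analyses: sitting time at 12 months, compared between arms by ANCOVA adjusted for baseline sitting time. State that any further covariates are taken at their baseline values. Make the mixed-design ANOVA over four time-points secondary.

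Then align the three places. The abstract should name the same primary method. Sample size calculations should say that 112 per arm was computed for 12-month values with SD 200 and is conservative for the ANCOVA. Data analyses should drop the change-score t-test as the 12-month comparison.

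The cost is wording only. Baseline sitting time is already collected, no extra patients or visits are needed, and 300 randomised remains sufficient at any non-negative r.

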### Design

The ‘TRIPL-A’ is a randomized, controlled, open, bicenter trial, with two parallel groups. The study will be carried out in two urban areas (independent in terms of staff, facilities and participants) in the Marche region (Central Italy): the Diabetology Unit of the IRCCS-INRCA Hospital in Ancona and the Diabetology Unit of the ASUR Hospital of Fabriano (AN). Enrolled patients will be assigned to either the intervention or control arm. The assessments will be performed within the medical facilities, while the exercise training program will be carried out within third party fitness facilities. An overview of the study is shown in Fig. 1.

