### Enrollment and arm assignment

A total of 300 older T2D patients will be enrolled and randomly assigned to either the control or the intervention arm with a 1:1 ratio, using a computerized permuted blocks randomization. The randomizations will be performed using a code created by the statisticians of the INRCA Biostatistical Center, who will not be involved in any other part of the trial. Allocation concealment will be assured because the trial staff will not know the randomization code and procedures (e.g., block sizes), and the allocation will be made only after the termination of all baseline tests (see Fig. 1).

Due to the obvious differences between the interventions (see below), neither staff nor participants will be blinded to group allocation. However, before data analysis, patient allocations and identification numbers will be replaced by categorical variables whose meaning will be unknown to data analysts.

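### The main 12-month comparison is a t-test that cannot hold a centre term in a two-centre trial; a model with arm and centre would be slightly more precise at almost no cost

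*Protocol article*

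**What the plan says.** The Design section of the protocol article describes a "randomized, controlled, open, bicenter trial, with two parallel groups", carried out in "two urban areas (independent in terms of staff, facilities and participants": Ancona and Fabriano.

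Under Enrollment and arm assignment, patients are allocated "with a 1:1 ratio, using a computerized permuted blocks randomization". The article does not say whether the blocks are formed within each centre or drawn from one common list.

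Assessments/outcomes makes the arm difference at 12 months the main outcome for each measure. Data analyses fixes how that difference is tested: "as the difference between baseline and 12-month time-point, using independent sample t-tests". The sample size rests on the same kind of test ("2-sided independent sample t-test; statistical power 0.8; α level of significance 0.05; 1:1 ratio between intervention and control arm").

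For the repeated-measures comparison over the four time-points, participants' characteristics enter the model: "e.g., age, sex, fitness status, physical activity level, and metabolic profile) will be used as covariates". Centre is not mentioned, but the items are given as examples only.

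**The concern.** The primary outcome is self-reported sitting time, collected by interview by staff who know the allocation. Counselling, interviewing and supervised training are done by different people in different places at the two centres. The average change over 12 months could therefore differ between Ancona and Fabriano for reasons unrelated to the arm. Centre is also known without error for every patient.

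An independent-samples t-test leaves any such difference in the error term. What follows depends on how the blocks were run:

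- **Blocks within centre.** The arms are balanced on centre by design, but the test's standard error ignores this and is a little too large.
- **One common list.** The standard error is right on average. However, the arms of the one trial actually run may differ by chance in centre mix, and the test does nothing about it.

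At stake is some precision in the main comparison. Its validity is not in question.

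**Working it through.** **Inputs.** From Sample size calculations: SD 200 min/day, difference 75 min/day, two-sided α 0.05, power 0.80, 112 per arm needed, 300 enrolled, 20% drop-out. The article gives neither the centre shares nor any centre difference, so both are assumed. D is the difference between centres in mean 12-month change, the same in both arms, taken as 0 to 100 min/day. q is one centre's share of patients, taken as 0.5 unless stated.

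**1. The plan's own figure.** n per arm = 2 × (1.96 + 0.8416)² × 200² / 75² = 111.6, so 112, as stated. A t-based calculation gives 112.6, which is the same up to rounding. Evaluable patients: 300 × 0.8 / 2 = 120 per arm. At 120 per arm the standard error is 200 × √(2/120) = 25.8 min, and power is Φ(75/25.8 − 1.96) = 0.828. The sample size is not in question.

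**2. What a centre term removes.** If the total SD is 200, the SD within centre is √(200² − q(1−q)D²). Replacing 200 by this value gives, at 120 per arm:

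| D (min/day) | q | SD within centre | Power with centre | n per arm for 80% |
|---|---|---|---|---|
| 0 | 0.5 | 200.0 | 0.828 | 112 |
| 50 | 0.5 | 198.4 | 0.833 | 110 |
| 75 | 0.5 | 196.5 | 0.841 | 108 |
| 100 | 0.5 | 193.6 | 0.851 | 105 |
| 100 | 0.2 | 196.0 | 0.842 | 108 |

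The largest gain in this range is 0.851 − 0.828 = 2.3 points. At D = 50 it is 0.5 points.

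**3. If blocks are run within centre.** The true variability of the arm difference follows the within-centre SD, but the t-test uses 200. Its actual two-sided type I error is 2 × P(Z > 1.97 × 200/193.6) = 0.042 at D = 100, and 2 × P(Z > 1.97 × 200/198.4) = 0.047 at D = 50. Simulations with 240 patients gave 0.043 to 0.048 at D = 100 and 0.045 to 0.052 at D = 50. The Monte Carlo error is about √(0.05 × 0.95/8000) = 0.002 for runs of 8,000. Under this allocation, power at D = 100 is 0.833 without centre and 0.848 with it (t-based), a gain of 1.5 points.

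**4. If one list serves both centres.** Simulated type I error of the t-test was 0.048 to 0.054, consistent with 0.05. The SD of the chance difference in centre share between arms is √(q(1−q) × 2/120) = 0.065 at q = 0.5, so the 95% range is about ±0.127. A simulation with an assumed block size of 4 put the 95th percentile of the absolute difference at 0.117 to 0.125. Taking 12 points, the estimate shifts by 0.12 × 50 = 6 min at D = 50, or 0.12 × 100 = 12 min at D = 100. The latter is 12/75 = 16% of the target difference and 12/25.8 = 0.46 standard errors.

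**5. Which D matters.** The analysed quantity is change from baseline. A stable difference between centres in sitting level or interviewing style cancels, so only a centre difference in change counts. The plan gives 200 as the SD of sitting time, not of change. With equal SDs at both times, the variance of change is 2 × 200² × (1 − ρ), which equals 200² when the baseline-to-12-month correlation ρ is 0.5. Applying 200 to change is therefore a further assumption.

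**The case against.** The strongest case against is that little is stated wrongly and the effect is slight.

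- **Silence in a condensed article.** Whether blocks were run per centre, and the full list of model terms, may stand in the full protocol or SAP. This is right for both of those items. It does not cover the 12-month test, which the article names and which cannot hold a centre term.
- **The repeated-measures model.** A reader might infer that its covariates ignore centre. The text does not support this: the list is open, and the Abstract plans repeated-measures ANCOVAs for each outcome. Centre is merely unnamed.
- **Bias.** A reader might infer that a centre difference leaks into the treatment effect. It does not. Under a common list, chance imbalance is random error that the t-test's standard error already includes. Under blocks within centre, the error is on the conservative side. What remains under a common list is an uncorrected shift in the single trial that is run.
- **Mismatch between design and analysis.** A reader might infer that a stratified randomisation is analysed without its stratum. The article does not say the randomisation was stratified, so no mismatch is shown.
- **Size.** Centre differences in change of 100 min/day or more exceed the whole 75 min target and are hard to believe. At 50 min the gain is half a power point, and power without centre is already above 0.80. This stands, and it is why the point is minor.

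**Conclusion.** The point holds as a small improvement in precision. The article fixes the main 12-month comparison as a test that cannot use centre, in a trial whose two centres share neither staff, facilities nor participants. The test is valid under a common list and mildly conservative under blocks within centre (type I error about 0.047 at a 50-min and 0.042 at a 100-min centre difference in change). Adding centre gains about 0 to 2 power points over assumed differences of 0 to 100 min/day, and it corrects a chance shift of about 6 to 12 min/day at the 95th percentile of imbalance for differences of 50 to 100 min/day.

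These figures rest on assumed centre differences and centre shares, on 120 evaluable patients per arm, and on applying the SD of 200 to the change score. The upper end of the range is unlikely. Neither the sample size nor the validity of the conclusions is affected.

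**What to change.** In Data analyses, replace the 12-month independent-samples t-test with a linear model for the 12-month change that contains arm and centre (Ancona or Fabriano) as fixed factors, for every outcome. Name centre as a fixed factor in the repeated-measures model as well. This is sensible whichever way the blocks were run.

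As a clarification only, state under Enrollment and arm assignment whether the permuted blocks were generated separately for each centre.

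The cost is a sentence or two of wording and one degree of freedom out of 240 − 2 = 238. No new data are needed and the sample size does not change.
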